### Statistical Analyses

Feasibility will be assessed through the analysis of data collected by the research team, including the number of participants screened and enrolled per month, the proportion of eligible participants who enroll in the study, the treatment-specific proportion of participants completing follow-up visits, rates of adherence to the intervention protocol, and fidelity of implementation measured by the percentage of domains captured by the NPs at each time point. Acceptability analysis will be based on descriptive statistics from the acceptability measures, such as simple means and percentages between treatment arms, and thematic analysis of qualitative data collected in postimplementation focus groups.

Meanwhile, preliminary efficacy analysis will assess the hypothesis that the iRaPID intervention will perform better than TAU over time using a primary outcome (ie, PrEP uptake) and secondary outcomes (ie, time to PrEP initiation, PrEP adherence and persistence). We will first test baseline characteristics for homogeneity between treatment arms using an independent-samples *t* test or Wilcoxon rank sum test (if unequal variances are assessed) for continuous variables and chi-square tests or Fisher exact tests (if any small cell sizes) for categorical variables. This analysis of baseline characteristics will be used to determine significantly different factors to include in the final model for adjustment. To assess our hypotheses relating to preliminary efficacy, we will use a generalized linear mixed model [78] with random subject effects to account for the correlation in repeated measurements that occur within subjects. Treatment assignment, time, and the interaction between time and treatment assignment, including confounders such as sociodemographic characteristics and prior PrEP or MOUD engagement, will be included as covariates. The proportion of participants that initiate PrEP will be estimated and compared using the linear contrast statement in SAS PROC GLIMMIX (SAS Institute). Similar analyses will be conducted for other outcomes, including MOUD uptake, time to PrEP initiation, optimal adherence to PrEP, and PrEP persistence.

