#### Informed Consent, Enrollment, and Randomization

After confirming eligibility criteria and providing informed consent, all participants underwent a baseline assessment, which took approximately 90 minutes and was administered electronically by a trained research staff member in a private room at NHSSP. Participants were then randomized (1:1) to receive either the iRaPID intervention or TAU. Randomization was done via REDCap software (Vanderbilt University), a secure, HIPAA (Health Insurance Portability and Accountability Act)-compliant web app with a built-in randomization feature that allows the development of a defined randomization model. Randomization was stratified by sex to ensure that an equal proportion of participants is present in both arms. Participants are assessed at baseline, and 1-, 3-, and 6-month time points. This approach allows us to examine short-term outcomes and the decay and emergence of intervention effects. Study participants are reimbursed for the time required to complete the assessments (US $35 for the baseline assessment and US $25 for each follow-up assessment).

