We will also estimate the preliminary efficacy of PrEP and MOUD uptake in this pilot RCT of the iRaPID intervention versus TAU (primary outcome). This will be determined by assessing PrEP and MOUD uptake (ie, current use). For those who initiate PrEP, we will also evaluate the time to PrEP initiation, along with adherence and persistence on PrEP, as part of the secondary outcome. Time to PrEP initiation will be calculated by recording the number of days between the first encounter with the NP or health care provider and the day of initiation of PrEP, validated by the pharmacy PrEP pick-up date. We will measure PrEP adherence using the visual analog scale [74] and confirm with dried blood spot testing [75-77]. Persistence on PrEP will be measured by assessing pharmacy data, including both refill (if refilled within 30 days after exhausting PrEP from previous fill or not) and pick-up information. Given the importance of moderating factors on the effect of efficacy, we will measure individual (eg, sociodemographic, sexually transmitted infection, drug use, depression), social (eg, social support), and structural (eg, stigma, physician distrust) factors at each in-depth interview.

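### The efficacy model has two unreconciled covariate rules, and the one driven by baseline significance tests should be dropped in favour of a short closed list

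*Protocol article*

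**What the plan says.** All of this is in the protocol article; no separate analysis plan is shown.

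- **Baseline tests** (Statistical Analyses): "We will first test baseline characteristics for homogeneity between treatment arms using an independent-samples" t test or a rank test for continuous variables, and chi-square or Fisher tests for categorical ones. The rank test is triggered by a variance condition: "Wilcoxon rank sum test (if unequal variances are assessed").
- **Rule 1, selection by test** (same section): "This analysis of baseline characteristics will be used to determine significantly different factors to include in the final model for adjustment".
- **Rule 2, open list** (same section, in the description of the mixed model): treatment, time and their interaction, "including confounders such as sociodemographic characteristics and prior PrEP or MOUD engagement, will be included as covariates". No test is attached to this list.
- **Allocation** (Informed Consent, Enrollment, and Randomization): "Participants were then randomized (1:1) to receive either the iRaPID intervention or TAU". Also: "Randomization was stratified by sex to ensure that an equal proportion of participants is present in both arms".
- **Candidate baseline factors** (Outcome Measures): "we will measure individual (eg, sociodemographic, sexually transmitted infection, drug use, depression), social (eg, social support), and structural (eg, stigma, physician distrust) factors". No count is given.

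Sex is not named as a model term, although it may be meant under the sociodemographic heading. Neither a significance level for the baseline tests nor the number of factors tested is stated.

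**The concern.** When allocation is random, any baseline difference between arms has arisen by chance, so a test of that difference answers no useful question. Whether a covariate belongs in the model depends on how strongly it predicts the outcome, and the baseline p-value carries no information on that. A rule that admits only significantly imbalanced variables therefore tends to admit irrelevant ones and pass over prognostic ones, and nobody can write down the final model before seeing the data.

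The open list softens this but does not settle it. The article does not say whether the list replaces the test rule, adds to it, or is filtered by it. Two analysts could follow the same paragraph and fit different models. The same ambiguity carries over to MOUD uptake, adherence and persistence, which are to be analysed in a similar way. At stake are power, which is scarce with 50 participants, and a reproducible estimate to carry into the future trial.

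**Working it through.** The plan gives no figure to reproduce on this point. The sample of 50 rests on a pilot rule of thumb, with no alpha, power or numeric effect.

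**Inputs from the article:** 50 participants randomised 1:1 (taken as 25 per arm); stratification by sex; 35 of 50 male, so 15 not male (Results).

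**Assumptions, because the article is silent:** baseline tests at two-sided 0.05; 5 to 20 factors tested; effect sizes as given below.

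**1. How often the rule adds something by chance.** With m independent tests under correct randomisation, P(at least one significant) = 1 − 0.95^m.

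| m | P(at least one) |
|---|---|
| 5 | 23% |
| 10 | 40% |
| 15 | 54% |
| 20 | 64% |

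The expected number of chance selections is 0.05 × m, for example 0.75 at m = 15 and 1.0 at m = 20. Real baseline factors are correlated, so these figures are a guide.

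**2. Whether the rule finds predictors.** One continuous covariate was simulated at 25 per arm with correlation 0.3, 0.5 or 0.7 to a continuous outcome. It was selected in about 5% of runs at every strength. Selection does not depend on prognostic value, so on its own the rule leaves a strong predictor out about 95% of the time.

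**3. Whether the rule would select sex.** Possible splits of 35 and 15 across two arms of 25:

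| Male/other, arm 1 v arm 2 | Fisher p | Chi-square p |
|---|---|---|
| 18/7 v 17/8 | 1.00 | 0.76 |
| 19/6 v 16/9 | 0.54 | 0.35 |
| 20/5 v 15/10 | 0.22 | 0.12 |

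Stratification aims at the first row, and even the third is not significant. Without stratification the selection probability would be 1.2% (Fisher) or 6.2% (chi-square); with it, essentially zero.

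**4. What the rule costs for a binary outcome.** PrEP uptake is binary, so the analogue is logistic regression at a single time point, 25 per arm, with an assumed treatment log odds ratio of 1.2 and one covariate:

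| Covariate log-OR per SD | Power, test-selected | Power, always adjusted | Difference (points) |
|---|---|---|---|
| 0.7 | 45% | 47% | 2 |
| 1.3 | 35% | 43% | 8 |
| 2.0 | 23% | 34% | 11 |

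Type I error was near or below 5% under both approaches. A repeat run for this write-up, with an assumed control-arm intercept of −1, agreed within about two points. Power is compared here, not the SD of the estimate: in a logistic model adjustment raises the SD (0.63 under the rule against 0.72 always adjusted at log-OR 0.7; 0.62 against 0.83 at 1.3), so SDs on the two scales are not comparable.

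**Side point.** The rank sum test is not a remedy for unequal variances, because its null distribution also assumes the two distributions are the same.

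**The case against.** The strongest reply is that the open list already does most of the work. It names prior PrEP or MOUD engagement, plausibly the best predictors of uptake, and sociodemographic characteristics, which ordinarily include sex. A reader might infer from the selection sentence alone that the final model will leave out the strong predictors and the stratification factor. The article does not support that: such omission follows from the test rule taken alone, and the list may well prevent it. This part of the objection stands, and it limits the point to a conflict between two rules, one of them unsound.

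A reader might also infer that the rule inflates false positives. It does not. In the linear analogue type I error fell (4.9%, 4.0% and 3.5% at correlations 0.3, 0.5 and 0.7), and in the binary analogue it stayed near or below 5%. The article states no error rate for the efficacy test that could be broken.

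A third tempting step is to turn a linear simulation into a sample-size penalty: at correlation 0.6, SDs of 0.270 and 0.229 give (0.270/0.229)² = 1.39. That conversion assumes a continuous outcome and does not carry over to binary uptake.

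Two further objections are fair in part. This is a pilot, and no confirmatory decision rests on the model. A fixed set can also use more terms than the rule adds on average (0.75 to 1.0 at 15 to 20 tests), so it must be kept short. Neither defends choosing covariates by baseline p-value. Nor is the point a detail left to an unseen analysis plan, because the article states the rule outright.

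**Conclusion.** The point holds in this form: the Statistical Analyses section gives two covariate rules that it does not reconcile, and the one based on baseline tests is unsound in a randomised trial. It selects by chance, ignores prognostic strength, makes the model data-dependent and would essentially never pick sex. Whether sex and the main predictors would in fact be omitted cannot be established, because the open list may cover them.

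Where the rule alone decides, the cost is lost power: about 2 points for a weak predictor and 8 to 11 for strong ones. Those figures rest on an assumed log odds ratio of 1.2, assumed covariate strengths, a 0.05 selection level and a single-time-point analogue of the planned mixed model, so they show the order of size only. The change is worth making before analysis, but in a pilot with preliminary efficacy aims it is a moderate matter.

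**What to change.** In Statistical Analyses:

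1. Delete the sentence that lets baseline tests choose covariates. Describe baseline characteristics by arm, without using p-values to select. This also removes the misplaced variance trigger for the rank sum test.
2. Replace the open list with a short closed set, fixed before the comparative analysis: sex, as the stratification factor, and prior PrEP and MOUD engagement, which the plan already names. The Limitations and Setbacks section itself says that being on treatment at enrolment can affect outcomes, which supports keeping that term whatever its baseline balance.
3. Report the unadjusted treatment estimate alongside the adjusted one.

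The cost is a change of wording, with no new data. On the article's timeline follow-up was due to finish by February 2023, so the set could be fixed before analysis. The downside is two or three degrees of freedom in a small logistic model, which is why the list should stay that short.

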### Sample Size

This study aims to test the feasibility and acceptability of the iRaPID program and obtain preliminary estimates of potential effects on HIV prevention outcomes among people who inject drugs. Previous research has shown that pilot studies of 20 to 30 participants per arm are considered adequate to meet proposed study aims similar to this study [79,80]. Our sample size of 50 participants would be ideal for detecting a moderate treatment effect and informing a future RCT. The recruitment of this sample size is feasible based on our formative work.

### Implementation Science Research

As previously mentioned, we are using a type I hybrid implementation trial design, where we will pilot test the NP-led iRaPID program while exploring multilevel implementation factors for future refinement and adoption. As such, we will conduct open-ended interviews with iRaPID participants (n=20) and relevant stakeholders (n=10), including recruitment staff, clinical providers, and administrators at the participating clinic.

We will administer a process measure to assess the overall satisfaction and perceived utility of each intervention component regarding organization-level factors (eg, perceived relevance of intervention components and characteristics to target population needs, the usefulness of the intervention to the organization, and barriers to intervention implementation as designed). These questions will elicit feedback about the potential barriers and facilitators to implementing the iRaPID program—as currently designed—regarding issues ranging from specific intervention components to the more general organizational dynamics (eg., time and resource constraints). The process evaluation will provide a nuanced understanding of the intervention effects, barriers, and facilitators to the intervention implementation and refinement needed to maximize implementation success in a real-world setting. Based on this feedback, the iRaPID program will then be adjusted and adapted for future implementation in various clinical settings.

## Results

Study recruitment began on July 28, 2021, and lasted until August 31, 2022. A total of 174 participants completed screening, yielding 99 eligible participants. The main reasons for ineligibility included not injecting drugs or not having ongoing HIV risk (eg, not engaging in risky sexual or injection drug use practices such as needle sharing). Among eligible participants, 85% (50/99) successfully enrolled in the study and were randomized to a study arm. The remaining eligible participants refused to participate in the study. Enrolled participants had a mean age of 45.98 (SD 8.19) years, 70% (35/50) were male, and 78% (39/50) identified as being heterosexual. They had a diverse portfolio of HIV risk behaviors, as most of them (47/50, 94%) had condomless sex in the past 6 months, and 84% (42/50) injected drugs in the past month. The final study follow-up is expected to be completed by February 2023, and the results will be available by mid-2023.

## Discussion

### Principal Findings and Implications

This ongoing trial aims to test an NP-led integrated HIV prevention program for people who inject drugs that combines same-day coprescribing of PrEP and MOUD. This strategy addresses delayed initiation and low linkage to HIV prevention (PrEP) and substance use (MOUD) care in traditional models. We hypothesize that the iRaPID intervention will be feasible and acceptable among people who inject drugs and will prove to be more efficacious than the standard of care for PrEP and MOUD services. We also anticipate that the results and qualitative feedback from participants and stakeholders will inform the refinement of the iRaPID intervention for a future large-scale RCT.

Same-day access to HIV preventive care may be particularly crucial for people who inject drugs with MOUD as they remain a hard-to-reach group and have significantly higher rates of attrition and poor linkage to care. Since HIV acquisition risk persists during delays, timely PrEP and MOUD initiation are critical in at-risk populations. Individuals with streamlined care initiation may also experience enhanced self-efficacy, encouraging continued engagement. Hence, our results could impact local and international PrEP and MOUD scale-up policies and promote engagement in HIV prevention services.

Given the risk of continued HIV outbreaks amidst the ongoing opioid crisis, scaling up PrEP alongside MOUD for people who inject drugs is crucial for HIV prevention. If successful, subsequent stand-alone tailored programs can be developed to support communities where opioid use is high and HIV outbreaks are likely, thereby promoting a transition to integrative care. Considering the limited access to and scale-up of harm-reduction strategies among people who inject drugs and the existing multilevel barriers to PrEP uptake, effective interventions are urgently needed to fill this critical gap. Given the significant growth in the waivered NP workforce, trained nurses are ideally situated to deliver this integrated care model. The iRaPID program represents a paradigm shift in HIV prevention and may be a particularly crucial strategy for people who inject drugs with OUD, as they remain an easy-to-miss subgroup with high rates of loss to follow-up and poor linkage to care.

### Limitations and Setbacks

The pilot trial has several limitations. Our study is restricted to 1 geographical location (Greater New Haven area, CT), potentially limiting the generalizability of our findings to all people who inject drugs across different geographic settings, particularly areas with fewer or absent SSPs. Further, the prescribing privileges of NPs have geographical disparities of their own, as they only have fully independent practice authority in 29 US commonwealths, states, and territories [81], which undermines nationwide program implementation in areas with physician shortages. Additionally, the study relies on self-reported measures of prior drug use, HIV-related risk behaviors, sexual behaviors, and some measures of primary outcomes (eg, adherence to PrEP using the visual analog scale). Impression management might occur to heighten protocol eligibility, which could potentially lead to the overreporting of risk behaviors during screening and subsequent discrepancies between data collected at different time points. Participants in the pilot trial include both out-of-treatment and in-treatment people who inject drugs (ie, those who were on BMT or MMT at the time of enrollment), which can affect treatment and adherence outcomes, especially as participants who were already on BMT or MMT at the time of enrollment did not undergo induction as compared to their out-of-treatment counterparts.

We also encountered many setbacks regarding participant recruitment due to the COVID-19 pandemic and the recurrent surge of cases in the area. Due to the nature of our program mandating in-person laboratory tests and assessments, ensuing research laboratory closures, and programmatic policies and changes that were developed to ensure research staff safety at the workplace (such as shift schedule changes and remote work) negatively affected recruitment efforts.

### Future Directions

Although shutdown conditions were lifted, insightful strategies implemented by the Addiction Medicine Program at Yale during the COVID-19 pandemic and grasped by the research and clinical staff for future potential use included establishing safe pick-up and delivery of medication and setting up telehealth access for patients. Comparably, the centralization of PrEP dispensing to clinical settings and the in-person nature of its delivery prompted a recent call in the literature for the integration of telehealth to alleviate patient- and provider-level demands [82]. Recent studies, especially in the context of the COVID-19 pandemic, established the feasibility of PrEP and MOUD delivery among people who inject drugs via telehealth [82,83]. Integrating telehealth services within harm reduction settings (eg, SSPs) could not only boost access and address demands imposed on patients [84-86] but also relieve some of the excess pressures imposed on people who inject drugs specifically, including logistical barriers to in-person care and concerns related to stigma. Future directions in implementing the iRaPID program also include expanding access to newly available HIV prevention tools. Preliminary trials have shown that the new Federal Drug Administration–approved, long-acting injectable cabotegravir (given intramuscularly every 8 weeks) is likely to be superior to daily oral tenofovir disoproxil fumarate-emtricitabine (marketed under the name Truvada) in at-risk cisgender men who have sex with men [87]. With the advent of a new mode of administration for PrEP and its ensuing impact on HIV prevention strategies and adherence rates, the iRaPID program will likely have to be restructured to include a long-acting injectable option for participants.

## Appendix

Multimedia Appendix 1 External Peer Review Report from the Population and Public Health Approaches to HIV/AIDS (PPAH) Study Section - Exploratory/Developmental Grants (R21) - National Institute on Drug Abuse (NIDA) (National Institutes of Health, USA).

## Abbreviations

BMT: buprenorphine maintenance therapy
HIPAA: Health Insurance Portability and Accountability Act
iRaPID: integrated rapid access to HIV prevention program for people who inject drugs
MMT: methadone maintenance therapy
MOUD: medication for opioid use disorder
NHSSP: New Haven Syringe Service Program
NP: nurse practitioner
PrEP: pre-exposure prophylaxis
RCT: randomized controlled trial
SSP: syringe services program
TAU: treatment as usual
